### Secondary outcomes

A questionnaire will be used to collect data on the secondary outcomes of interest at baseline and follow-up (*t*
_3_). Validated tools used to measure these endpoints will be included in the questionnaires with approval from their respective developers.

#### Adherence

Change in self-reported medication adherence will be examined using the eight-question Morisky Medication Adherence Scale (MMAS-8) [20–22] and patient interview. The MMAS-8 has been validated extensively in other chronic diseases and multiple languages worldwide [21–23]. It contains seven questions with yes/no alternatives and one question that features a 5-point Likert scale. Adherence scores can range from 0 to 8 and may be trichotomized into high (score 8), medium (score 6 to <8), and low (score <6) adherence rankings.

#### Quality of life

The Chronic Liver Disease Questionnaire (CLDQ) [24] is a widely used health-related QoL tool that has been validated in numerous etiologies and severities of CLD and in several languages [24–29]. The CLDQ asks patients to rank a series of symptoms, impacts on daily activities, and mood disturbances for frequency of occurrence using a 7-point Likert scale, where a higher score indicates a better QoL. It includes 29 items across 6 domains: 8 questions related to emotional function; 3 questions related to abdominal symptoms; 3 questions related to activity; and 5 questions within each of the domains of systemic symptoms, fatigue, and worry.

#### Medication beliefs

Beliefs about medications will be examined using the Beliefs about Medicines Questionnaires (BMQ-General and BMQ-Specific) [30], which contain a series of statements about medications. Patients are required to indicate the extent of their personal agreement or disagreement with each statement using a 5-point Likert scale. The BMQ-General contains four items related to the overuse of medicines and four items about medication harmfulness. The BMQ-Specific contains five items about “necessity” beliefs and five items about “concerns” that patients may have about their medicines. The internal consistency, discriminant validity, and correlation of the BMQ with other clinical measures are described elsewhere [30–32].

#### Illness perceptions

The Brief Illness Perception Questionnaire [33] will be used to examine changes in patients’ perceptions about cirrhosis. The questionnaire has proven validity and correlation with outcomes in numerous chronic diseases [33, 34]. It contains eight items that patients rank from 0 to 10 related to their perception of disease and medicines. Patients are also asked to identify three important factors that they believe caused their current illness.

#### Cirrhosis and lifestyle knowledge

Knowledge of cirrhosis self-management tasks related to decompensation history and prescribed medications will be determined via questionnaire (using the same questions pre- and postintervention). Eight questions related to over-the-counter analgesia, management of ascites and sodium restriction, and monitoring of weight and blood pressure have been incorporated into the surveys, adapted from Volk et al. [3].

#### Hospitalization and mortality

The number of hospital admissions, including the frequency of abdominal paracenteses in patients with ascites, will be derived from medical records. Hospitalizations for liver-related and non-liver-related events in the 2 years preceding recruitment and 12 months following recruitment, including data on patients’ clinical decompensation prior to enrollment and postenrollment (e.g., date, type and severity of decompensation event, new or recurrent event) will be collected. Follow-up will be conducted at 12 months and again at 3 years. Frequency and duration of hospitalization for management of cirrhosis-related and non-cirrhosis-related complications, cirrhosis-related mortality, and non-cirrhosis-related mortality will be interpreted within the context of patients’ liver disease severity, decompensation history, development of new decompensation events, and other prognostic and clinical variables.

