#### Hypotheses

Compared with patients receiving usual care, patients who receive the tailored (additional) education and medication management intervention are hypothesized to benefit in the following ways:

(H1) Fewer medication discrepancies

(H2) Improved medication adherence

(H3) Improved QoL

(H4) Improved illness perceptions

(H5) Improved medication beliefs

(H6) Improved knowledge of disease self-management tasks related to prescribed medications

(H7) Fewer hospital admissions

(H8) Longer survival time

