### Study endpoints and data collection

Study outcomes, tools, and time points for measurement are outlined in Table 3. Follow-up will occur approximately 6 months post-enrollment (allowed range 140–224 days after baseline interview), according to outpatient hepatology scheduling availability. If a follow-up appointment is missed, a second appointment will be offered to the patient within the allowed time frame. If the second appointment is missed, the patient will be considered lost to follow-up for *t*
_3_ survey endpoints.

**Table 3 Tab3:** Outcomes and other measures of the medication management and education intervention

Categories/variables	Measure	Collection week
Medication discrepancies		
Between drug name and dosage Frequency of per-patient discrepancies Severity of discrepancies	Patient interview Questionnaire Medical record review	*t* _0,_ *t* _3_
Medication-related problems (intervention arm only)		
Adverse drug reaction Drug interaction Untreated, undertreated, or overtreated indication Other medication-related barriers	Patient interview Questionnaire	*t* _0,_ *t* _3_
Adherence		
Self-reported medication adherence Affordability	MMAS-8 Patient interview	*t* _0,_ *t* _3_
Quality of life		
Health-related quality of life Abdominal and systemic symptoms Emotional functioning, fatigue, and worry Daily activity	CLDQ Brief IPQ	*t* _0,_ *t* _3_
Beliefs and perceptions		
General medication beliefs Beliefs about liver disease medications Illness perceptions	BMQ-General BMQ-Specific Brief IPQ	*t* _0,_ *t* _3_
Knowledge/health literacy		
Knowledge of causation Dietary modification including sodium restriction Self-monitoring requirements Safe analgesia Source of medication-related information	Questionnaire Brief IPQ	*t* _0,_ *t* _3_
Hospitalization		
Liver-related hospitalization Non-liver-related hospitalization Duration of stay	Medical record review	*t* _3,_ *t* _4_ (and 3 years)
Survival		
Liver-related mortality Non-liver-related mortality	Medical record review	*t* _3,_ *t* _4_ (and 3 years)
Cost		
Cost of service implementation Potential cost savings	Cost modeling	After study completion

*Abbreviations: BMQ* Beliefs about Medicines Questionnaire, *Brief IPQ* Brief Illness Perception Questionnaire, *CLDQ* Chronic Liver Disease Questionnaire, *MMAS-8* Eight-question Morisky Medication Adherence Scale

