### Data analysis

Data will be coded and stored in a password-protected database and analyzed using a statistical software package (IBM SPSS Statistics version 20.0; IBM, Armonk, NY, USA). Study endpoints experienced for each treatment group will be formally analyzed on an intention-to-treat basis [36]. Important potential confounders will be included in a secondary multivariate analysis (e.g., hospital admission, mortality). Post hoc subgroup analysis will be used to further explore outcomes according to the intensity of the intervention and completeness of relevant personalized education received by intervention participants.

The study endpoints will be presented quantitatively (proportions, statistical differences between groups) and qualitatively (description of discrepancies, MRPs, and some patient-reported medication beliefs and illness perceptions). All tests will be two-tailed, and significance will be set at α = 0.05. Continuous and normally-distributed variables will be presented as mean ± SD. Differences between groups will be analyzed using one-way analysis of variance. Non-normally distributed data will be presented as median (range), and nonparametric tests will be used to analyze differences between groups. Categorical data will be analyzed using Pearson’s chi-square test or Fisher’s exact test. Pearson’s correlation or Spearman’s rank correlation coefficient will be used to identify linear relationships between normally distributed and non-normally distributed continuous variables, respectively.

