### Power calculation and sample size determination

On the basis of a primary endpoint of a 50% reduction in medication discrepancies (3.12 ± 2.5 per patient [6] to 1.56 per patient), 41 participants will be required per treatment arm to achieve ≥80% statistical power. Median survival in decompensated cirrhosis is 2 years [37]. Therefore, a 6-month mortality rate between 10% and 15% among the study cohort is predicted. The Hepatology Outpatient Centre’s attendance failure/reschedule rate is approximately 20%. Therefore, a possible 30% loss will be accounted for, and at least 106 participants will be recruited.

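### Total admissions and bed-days (H7) have no stated method that accounts for time alive, so if the intervention also prolongs survival (H8) unadjusted counts understate a fall in the admission rate

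*Protocol article*

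**What the plan says.** Among the secondary hypotheses of the protocol article, H7 expects fewer hospital admissions and H8 longer survival. The section Hospitalization and mortality takes the number of admissions from medical records and will interpret "Frequency and duration of hospitalization for management of cirrhosis-related and non-cirrhosis-related complications" in the light of disease severity and prognosis. The records cover "Hospitalizations for liver-related and non-liver-related events in the 2 years preceding recruitment and 12 months following recruitment", with a further follow-up at 3 years. Table 3 lists hospitalization at t3, t4 and 3 years.

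Data analysis gives one general rule for comparing arms: one-way analysis of variance for normally distributed variables, and for the rest "nonparametric tests will be used to analyze differences between groups". "All tests will be two-tailed", and "significance will be set at α = 0.05".

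The time-to-event paragraph counts person-time from recruitment to death or 12 months, whichever is earlier. It plans a competing-risks analysis with three separate events: first cirrhosis-related readmission, death from cirrhosis, and death from other causes.

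Data analysis also lists hospitalization frequency among the baseline variables that may influence endpoints, and says clinically significant baseline differences between arms will be adjusted for.

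The sample size section states that "Median survival in decompensated cirrhosis is 2 years" and predicts 10% to 15% mortality at 6 months.

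**The concern.** Death ends a patient's admission count. A patient who dies in the first month without an admission and one who lives the full year without an admission both score zero, although their exposure differs greatly. The general tests make no allowance for this.

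The planned competing-risks analysis does handle death, but only for the first cirrhosis-related readmission. The Background section puts admissions at about three a year, so much of what H7 counts comes later. Repeat admissions, non-liver admissions and days in hospital have no stated treatment of death.

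H7 and H8 can therefore pull against each other. If the intervention keeps more patients alive, those patients go on being admitted, and a genuine fall in the admission rate shrinks or disappears in the totals. The 3-year comparison is the more exposed, because more patients will have died by then and the stated person-time rule stops at 12 months.

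**Working it through.** **Inputs from the protocol article.** Median survival of 2 years, predicted 6-month mortality of 10–15%, and at least 106 participants recruited, taken as 53 per arm (Power calculation and sample size determination); about three admissions a year (Background); alpha 0.05, two-sided (Data analysis). The article gives no sample size or power for H7, so there is no planned figure to reproduce.

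**Assumptions, not in the article.** Constant hazard of death; mortality hazard ratio (HR) 0.8, 0.7 or 0.5; gamma variation between patients in admission rate, with variance 0.5 or 1.

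**1. Mortality at 12 months.**
- From the 2-year median: 1 − 0.5^(1/2) = 29.3%. The same median gives 1 − 0.5^(1/4) = 15.9% at 6 months, slightly above the article's own range.
- From 10–15% at 6 months: 1 − 0.90² = 19.0% and 1 − 0.85² = 27.8%.
- The range is therefore 19–29%, and 29% is its upper end.

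**2. Time alive.** Mean time alive over T years with hazard h is (1 − e^(−hT))/h. For the 2-year median, h = ln 2 / 2 = 0.3466.

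| Window | Control | HR 0.8 | HR 0.7 | HR 0.5 |
|---|---|---|---|---|
| 12 months, mean years alive | 0.845 | 0.873 | 0.888 | 0.918 |
| Ratio to control | 1 | 1.033 | 1.051 | 1.086 |
| 3 years, mean years alive | 1.865 | 2.037 | 2.131 | 2.340 |
| Ratio to control | 1 | 1.092 | 1.143 | 1.254 |

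Mortality at 3 years in the control arm is 1 − 0.5^(3/2) = 64.6%.

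**3. Effect on the count ratio.** If the admission rate does not depend on the risk of death, the expected ratio of mean counts is the true rate ratio times the ratio of time alive. For a true rate ratio of 0.90:
- 12 months: 0.90 × 1.033 = 0.93; 0.90 × 1.051 = 0.95; 0.90 × 1.086 = 0.98.
- 3 years: 0.90 × 1.092 = 0.98; 0.90 × 1.143 = 1.03; 0.90 × 1.254 = 1.13.

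With HR 1 every ratio of time alive is 1, and the count ratio stays at 0.90.

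**4. Lower mortality.** With 10% dead at 6 months, h = −2 ln 0.90 = 0.2107. The ratios of time alive for HR 0.8 to 0.5 become 1.02 to 1.05 at 12 months and 1.06 to 1.16 at 3 years. A true 10% fall at 3 years then appears as 0.95 to 1.04.

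**5. Power at 12 months, by simulation** (53 per arm, three admissions a year in controls). Only the step from the second to the third column of figures is due to exposure.

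| Setting | Rank test on counts | Negative binomial, no offset | Negative binomial, log time-alive offset |
|---|---|---|---|
| Rate ratio 0.6, HR 0.7, variance 1 | 28% | 42% | 55% |
| Rate ratio 0.6, HR 1, variance 1 | 40% | 52% | 57% |
| Rate ratio 0.7, HR 0.7, variance 0.5 | 24% | 34% | 45% |
| Rate ratio 0.7, HR 1, variance 0.5 | 31% | 39% | 43% |

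The offset adds 4–5 points when survival is equal and 11–13 points at HR 0.7. Type I error of the offset model was 5–7% in the simulations, so a small part of the gain is inflation. In the first setting, adding prior admissions as a covariate raised power to about 81%, provided the same patient-level tendency drives past and future admissions.

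**The case against.** The article never says that admissions will be compared as raw counts. Its explicit per-patient count comparison concerns medication discrepancies, and the model for a secondary count outcome could sit in an analysis plan that is not shown. This stands as a limit: the method is inferred from the general rule. But the article does set out its tests, and none of those that fit this endpoint takes account of time alive. The person-time rule and the competing-risks analysis serve the survival analyses and the first cirrhosis-related readmission; they supply no rate for totals.

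H7 is a secondary aim, which the article frames as descriptive, and it is unpowered. That limits the consequences.

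Three stronger readings are tempting, and the documents do not support them.
- A reader might infer that the t3 window ("allowed range 140–224 days after baseline interview") distorts the main comparison. That range governs the follow-up appointment, and missing it means loss for survey endpoints. Admissions come from records over a fixed 12 months. What remains is only that no cut-off day is given for the t3 count.
- A reader might infer that prior admissions go unused. They would be adjusted for if the arms differ to a clinically significant degree at baseline. The weakness is that the adjustment is conditional.
- A reader might put the whole power gap between the rank test and the offset model down to death. With equal survival, most of it comes from replacing the rank test.

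The remedy is also imperfect. The calculations in steps 2 and 3 treat death and admission as independent. In a simulation where sicker patients both died and were admitted more (HR 0.7, true rate ratio 0.90), the crude ratio was 0.98 and the ratio per time alive 0.94, so the offset removed only part of the bias.

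**Conclusion.** The point holds in a conditional form. No stated method for total admissions or bed-days accounts for time alive, although the article's own figures imply 19–29% deaths by 12 months under constant hazard. With equal survival there is no bias, only lost efficiency. If the intervention prolongs survival, unadjusted counts understate a fall in the admission rate. For a 2-year median and an assumed mortality HR of 0.8–0.5, the count ratio is inflated by 3–9% at 12 months (2–5% at the lowest mortality the article predicts) and by 9–25% at 3 years. The 12-month distortion is modest. At 3 years it can turn a true 10% fall into little change or an apparent rise. The HR values and the degree of variation between patients are assumptions, not figures from the article.

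**What to change.** State in Data analysis that:
- Admissions and days in hospital are analysed over fixed windows from recruitment: 12 months, 3 years, and a fixed day for any t3 count.
- They are compared as rates per time alive, for example with a negative binomial model with log(days alive in the window) as offset.
- Admissions in the 2 years before recruitment enter as a prespecified covariate, not only when the arms differ at baseline.
- The result is reported beside mortality and the planned competing-risks analysis, with a note that the offset removes only part of the bias if sicker patients both die and are admitted more.

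This costs analysis wording only. Admission histories and dates of death are already to be taken from medical records, and no extra patients or visits are needed.

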#### Medication-related problems

Intervention participants may have MRPs identified during their interview that warrant follow-up action or monitoring. The pharmacist will document the types of MRPs identified, the action or monitoring required, and the steps taken toward resolution in patients’ medical records and using the structured data collection tool. This information will not be available for usual care participants, because they will not have a medication review. The change in frequency (count) and potential harm (risk matrix) of MRPs will be assessed using an equivalent time sample where the intervention group is its own control. The clinical significance of MRPs will be determined by blinded comparison at the completion of the study using a risk matrix tool (Fig. 2), as described in the Methods subsection “Medication-related problems” above.

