In existing models of collaborative outpatient practice, integrated pharmacist education and medication management interventions have been shown to improve patient knowledge, adherence, and outcomes in chronic diseases that have complex medication management issues similar to those of cirrhosis [9–13]. Identification of medication discrepancies and MRPs using a clinical pharmacist’s reconciled medication record reduces harm and hospitalization and may allow for simplification of the prescribed regimen [14, 15]. The association between patient knowledge, polypharmacy, poor adherence, and medication discrepancies has not been investigated in patients with decompensated cirrhosis to date. It is hypothesized that addressing this complicated relationship by implementing a targeted patient education and medication management intervention in a multidisciplinary model of hepatology ambulatory care may improve medication management, reduce MRPs, and improve medication-related outcomes for people with decompensated disease.

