**Fig. 1 Fig1:**
[figure not shown]
Standard Protocol Items: Recommendations for Interventional Trials (SPIRIT) flow diagram of participant recruitment and study navigation. *MRP* Medication-related problem

All participants will complete a baseline survey prior to their scheduled outpatient clinic review. Validated questionnaire tools will be used to determine baseline medication adherence, medication beliefs, illness perceptions, and QoL, in addition to patient knowledge of important dietary and lifestyle modifications. The survey will be completed with a study coordinator over the telephone or in person in a private clinic room, or it will be self-completed by the participant in the clinic waiting room. Patient carers or family members will be involved if necessary.

Usual care participants will subsequently receive routine review and education by their hepatologist according to the current model of care in the hepatology clinic. Intervention participants will be reviewed by a clinical pharmacist to receive the education and medication management intervention (described below) in addition to routine review and education by their hepatologist. Intervention participants will also receive three further educational contacts from the clinical pharmacist in addition to scheduled routine hepatologist review within the following 6-month period.

All participants will be resurveyed at follow-up (*t*
_3_, approximately 6 months post-enrollment) to explore changes in their medication adherence, medication beliefs, illness perceptions, QoL, and knowledge. Patient outcome data will be collected at 52 weeks (*see* “Study endpoints and data collection” section below).

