### Intervention description

During the initial encounter with each intervention patient (and carer/family member if present), the clinical pharmacist will obtain a complete, reconciled list of current medications and identify MRPs. The pharmacist will use open and closed questions to ascertain adherence, other medication-taking behaviors, and medication needs on an individualized basis. Participating patients will receive medication- and lifestyle-related education and advice tailored to their needs (decompensation history and medications) and receptiveness (Table 2). The pharmacist will also collaborate with the patient’s general practitioner and hepatologist to optimize therapy, facilitate resolution of MRPs, and monitor issues where required.

Subsequent contact with participants will be made at 4–6 weeks (*t*
_1_) and 12–14 weeks (*t*
_2_) after the baseline interview to discuss changes in prescribed therapy; identify new MRPs and previously identified MRPs that are ongoing; reiterate advice provided at baseline; and provide additional relevant education about medications, lifestyle modifications, and self-management of cirrhosis to build on previous discussions. Promotion of a patient-clinician partnership will be central to each discussion to encourage functional health literacy and self-efficacy with regard to patient confidence to raise questions and discuss issues with health care providers.

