### Medication-related problems

During patient interviews, the clinical pharmacist will identify actual and potential MRPs and document these in the patients’ medical notes and on a structured data collection form. The pharmacist will then facilitate the resolution or monitoring of individual MRPs with other relevant clinicians as appropriate and document each outcome in patients’ medical notes and data collection forms.

The clinical significance of MRPs (and medication discrepancies) will be assessed by a clinician panel using a risk matrix (Fig. 2) modified from the Metro North Health Service Risk Management Framework [19]. The matrix assigns a composite risk of prospective severity and likelihood of potential harm, as well as duration of time until potential harm may occur, as a consequence of the MRP. The panel of clinicians will comprise at least one clinical pharmacist, hepatologist, and general physician/pharmacologist who have experience in managing patients with cirrhosis. MRPs will be de-identified, randomized, and independently assessed by at least two members of the panel. Relevant clinical information will accompany the de-identified MRPs, but not details of patient outcomes or MRP resolution, to ensure unbiased prospective assessment of potential harm. Consensus of individual rankings will be used to determine the final measure of potential harm. Where there is disagreement between individual rankings, a roundtable panel discussion will be called to facilitate consensus.

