Time to first episode of decompensation and time to death (cause-specific and all-cause) will be assessed using Kaplan-Meier survival curves. The curves will be compared with the log-rank test statistic. Cox proportional hazards modeling will be used to calculate HRs, after testing the proportional hazards assumption. Patients will contribute person-time from the date of recruitment until the earliest of end of follow-up (12 months) or death (date of death to be obtained from medical records). Competing risks analysis will be performed in which we encode, as separate events, time to first readmission with a cirrhosis-related episode, death resulting from cirrhosis, or death resulting from other causes. This will be extended to multivariate analysis if there are a sufficient number of events.

It is anticipated that a proportion of participants (approximately 30%) will be lost from the study before completing follow-up assessments at *t*
_3_. Although the sample size calculation has been adjusted to accommodate for this loss, subjects who have completed only one assessment will be included in the analyses to establish baseline parameters in both treatment groups. With respect to changes from baseline, data imputation will be considered. In decompensated cirrhosis, dropouts due to death are informatively censored, and thus the responses of patients with missing data will be modeled explicitly. Subjects will be matched using baseline demographic and patient-reported outcomes, repeating this technique for both intervention arms. Imputation methods such as a hot-deck imputation and iterative regression imputation will be used. The sensitivity of the results to each of these methods will be assessed to quantify the degree of bias present.

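### The medication-related problem analysis is an uncontrolled before-after comparison under the wrong design label, so a change in either direction cannot be credited to the intervention

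*Protocol article*

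**What the plan says.** The Medication-related problems subsection under Secondary outcomes fixes the method: the change in count and in potential harm "of MRPs will be assessed using an equivalent time sample where the intervention group is its own control". It explains why only one arm contributes: "This information will not be available for usual care participants, because they will not have a medication review". Table 3 (Study endpoints and data collection) carries the row "Medication-related problems (intervention arm only", with t0 and t3 as its collection times.

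On exposure, Study navigation says: "Intervention participants will also receive three further educational contacts from the clinical pharmacist in addition to scheduled routine hepatologist review". These contacts follow the baseline encounter and fall within six months. The Intervention description places two of them at 4–6 weeks (t1) and 12–14 weeks (t2), when the pharmacist is to "identify new MRPs and previously identified MRPs that are ongoing".

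On who counts, the Medication-related problems subsection earlier in the Methods says that "the clinical pharmacist will identify actual and potential MRPs and document these in the patients’ medical notes and on a structured data collection form". A panel working from de-identified records then rates potential harm.

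On what is expected, the Background hypothesises that the intervention "may improve medication management, reduce MRPs, and improve medication-related outcomes for people with decompensated disease". On loss, the Data analysis section anticipates that a proportion of participants ("approximately 30%) will be lost from the study before completing follow-up assessments at" t3. It treats dropout through death as informative.

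**The concern.** An equivalent time-samples design gains its strength from repeated alternation of treated and untreated periods in the same group, with measurement in each. That alternation is what lets a single group serve as its own control. Nothing of the kind is described here. With treatment continuous from t0, two measurements and no MRP data from usual care, the plan is a one-group before-after comparison under the name of a stronger design.

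Such a comparison cannot separate the intervention from other sources of change: routine hepatologist care, the course of the disease, selective loss, or changes in how the pharmacist detects and records problems. The article sits within a randomised trial, and its Limitations section does not say that a change in MRPs cannot be attributed to the intervention. A reader told that the arm is its own control may make that attribution. What is at stake is the conclusion about MRPs, not the primary result.

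**Working it through.** **Plan's own figures.** The article gives no mean, SD, sample size or power for MRPs. Its sample size concerns discrepancies: 2 × (1.96 + 0.84)² × 2.5² / 1.56² ≈ 40.3, so 41 per arm, as stated. It serves here only to set the arm size: 106 / 2 = 53 recruited, and 53 × 0.7 ≈ 37 with t3 data.

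**Label against design.**
- Alternating periods on and off treatment: required by the label; none described.
- Repeated measurements in each condition: required by the label; Table 3 lists t0 and t3 only. MRPs are identified at t1 and t2, but those are also treated time points.
- Concurrent control: none, as the article says openly.

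**Effect of loss, with no intervention effect.** Let those who stay average 1 MRP (in relative units) and those lost average r, with 30% lost. Compare all baseline patients with t3 completers:
- baseline mean = 0.7 + 0.3r; t3 mean = 1; fall in mean = 0.3(r − 1) / (0.7 + 0.3r)
- baseline total per enrolled patient = 0.7 + 0.3r; t3 total = 0.7; fall in total = 0.3r / (0.7 + 0.3r)

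| r (assumed) | Fall in mean | Fall in total |
|---|---|---|
| 1 | 0% | 0.3 / 1 = 30% |
| 1.5 | 0.15 / 1.15 = 13.0% | 0.45 / 1.15 = 39.1% |
| 2 | 0.3 / 1.3 = 23.1% | 0.6 / 1.3 = 46.2% |

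In the same patients at both times, those who stay average 1 at t0 and 1 at t3, so this fall disappears. A simulation agrees (53 patients, 37 retained, assumed mean of 3 MRPs with gamma-Poisson variation). Preferential loss of patients with more MRPs gave an apparent fall of about 8% to 16% against all baseline patients, and about 0% in paired completers.

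**Effect of the counting rule.** Let B be the problems present at t0, U those of them still unresolved at t3, and N the new ones present at t3. If t3 counts everything present, it is U + N, the same kind of quantity as B. If nothing is resolved, U = B and the count cannot fall. If t3 counts only new problems, the change is N − B, which can be negative with no effect at all. The new-and-ongoing wording applies to t1 and t2; no counting rule is given for t3.

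**Effect of background change.** Simulation with no intervention effect, 37 paired completers, the same assumed count distribution, and a two-sided test at 0.05:

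| Background change in MRPs | Chance of a significant fall, one arm | Chance of any observed fall |
|---|---|---|
| +20% | 0.0% | 8% |
| 0% | 2.6% | 49% |
| −10% | 11% | 77% |
| −20% | 33% | 94% |
| −30% | 64% | 99% |
| −40% | 89% | over 99% |

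Had changes been compared between two arms, the two-sided false-positive rate would have stayed at 4% to 6% in every row. The one-arm result is thus governed by a background trend that the trial does not measure for MRPs.

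**The case against.** A reader might infer that MRPs are bound to fall even if the intervention does nothing. The documents do not support that.
- The Background says that regimens grow or change with repeated admissions, which would push problems up. Repeated review can also uncover more of them.
- Eligibility allows complications up to two years old, recruitment is at routine appointments, and nobody is selected on MRP count. Regression to the mean is therefore possible but not established.
- Being its own control most naturally means a within-patient comparison, where the loss figures largely vanish. Group totals are specified for discrepancies, not for MRPs.
- The ratio of 1.5 to 2 is assumed.

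The article is also partly open about the limits. It states that usual care has no MRP data and marks the Table 3 row accordingly. MRPs are absent from H1–H8 and from the Data analysis list of changes used to measure the intervention effect, and that section includes them under qualitative description. The harm rating is de-identified and made independently by at least two panel members, without details of resolution.

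All of this stands, and it limits the direction, size and importance of the point. It does not rescue the design label. Bias of unknown direction defeats a causal reading as surely as bias of known direction. The panel protects the harm rating but not the count, and the count is a named outcome. Pairing removes the loss artefact but not background change or changes in detection, and it confines the result to those who reach t3.

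**Conclusion.** The point holds in this form: the MRP analysis is an uncontrolled before-after comparison wrongly described as an equivalent time sample, and a change in either direction is not evidence of an intervention effect. This rests on the article's own description of exposure, time points and arms, and needs no assumed figure.

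The size of any spurious change is not fixed by the documents. The 30% fall in the group total needs only the planned loss and a comparison of all baseline patients with completers. The 13% to 23% fall in the mean also needs the assumed ratio of 1.5 to 2. The simulated chances of a significant fall depend on an assumed mean of 3, an assumed spread and an assumed background trend.

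Importance is limited. MRPs are a secondary outcome outside the formal hypotheses, and the primary endpoint is measured in both randomised arms.

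**What to change.** - Replace the equivalent-time-sample and own-control wording with a plain statement that MRPs are described before and after, in one arm, without a control.
- Compare t0 and t3 in the same patients under one counting rule, namely all problems present at each time. Show new, carried-over and resolved MRPs separately.
- State, there and in the Limitations, that the change is not evidence of an intervention effect, and that effect claims rest on the randomised comparison of discrepancies.

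The pharmacist already documents the type of each problem, the action needed and the steps towards resolution, so the change is one of wording and tabulation. This matters because the Trial status section reports recruitment as complete. The cost is that the trial gives up a causal claim about MRP reduction.
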